### Statistical analysis

All analyses will be conducted according to the intention-to-treat principle by blinded statisticians. All patients will be analyzed in accordance with the results of randomization, regardless of whether they received the prescribed therapy. Baseline characteristics between the groups will be reported as frequencies and percentages for categorical variables and as means and standard deviations (SD) or medians and interquartile ranges (IQR) for continuous variables. The primary outcome will be compared between the groups in a log-rank test. Other efficacy and safety endpoints will be reported with the *t* test or Wilcoxon test, and the chi-square test for continuous and categorial variables, respectively, as appropriate. All tests are two-sided, and the nominal level of *α* will be 5%.

In the subgroup analysis, age and ECPR will be defined by the presence or absence of a pre-randomization variable and the primary outcome as in the main analysis. The main analysis for each subgroup will be an unadjusted test of interaction in a logistic model to determine whether the effect of treatment differs significantly across categories. The missing values will not be imputed unless substantial. The number of observations used in the analysis will be reported.

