### Randomization

All eligible patients are centrally randomized in a 1:1 ratio to either early CRRT or conventional indication CRRT, and/or beta-blocker group or usual care (control) groups, via a computer-generated randomization schedule, stratified by age (< 65 vs. ≥ 65 years) and implantation of ECMO for extracorporeal cardiopulmonary resuscitation (yes vs no). The sequence of randomization is generated by an independent statistician, using SAS version 9.4. Investigators use a cellphone application to confirm eligibility and obtain the randomized treatment allocation.

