### Outcomes

The proportion of all-cause mortality at 30 days will be compared between the intervention and control groups. Survival data will be collected through telephone follow-up. Secondary outcomes are all-cause mortality at 365 days; use of long-term RRT; success in weaning from ECMO, defined as survival after 24 h from weaning; health-related quality of life according to scores on the EuroQoL (EQ-5D-5L) questionnaire at 365 days; length of stay at ICU and hospital; unplanned hospital readmission; and separately on cardiac and non-cardiac death.

Severe adverse events (SAEs), such as major bleeding, cardiac arrhythmias, ventilator-associated pneumonia, bloodstream infection, surgical site infection, limb ischemia from any cause, and ischemic or hematologic stroke will be collected systemically. Any other SAEs determined by the physicians through spontaneous reporting (Table 4 outlines SAE definitions). The publication will detail each documented SAE. All the SAEs will be coded through MedDRA.

**Table 4 Tab4:** Definition of SAEs

The SAEs include but are not limited to	
Major bleeding	
Bleeding requires transfusion for > 2 units	
Severe arrhythmias	
Type II second-degree AVB or third-degree AVB	
Sustained ventricular tachycardia (> 30 s)	
Ventricular fibrillation	
Ventilator associated pneumonia, which needs to meet all the criteria below:	
At least 48 h after endotracheal intubation	
Chest X-ray showing sustained or worsening shadowing (infiltrates or consolidations)	
Signs of pulmonary consolidation and/or crackles on auscultation, at least meet one of the following criteria:	
a) White blood cell count > 10 × 10^9^/L or < 4 × 10^9^/L	
b) Temperature > 37.5 °C, purulent secretions	
c) Positive cultures obtained directly from bronchial secretions	
Bloodstream infection	
Positive cultures obtained from the peripheral blood	
SSI	
Purulent drainage in the operated region with pain or tenderness, localized swelling, redness, and heat or fever, requiring operation, including superficial incisional wound SSI, deep incisional wound SSI, and organ/space SSI	
Limb ischemia from any cause	
Physical examination demonstrating pain, pallor, pulseless, cold, and motor or sensor deficit	
Requiring decannulation of ECMO catheter or surgical intervention	
Stroke	
New onset abnormal neurological signs and symptoms last for at least 24 h with radiographic evidence	
Any other severe adverse events determined by the physicians	

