### Sample size

Sample size calculation is performed using the software PASS 15.0.5 based on the following assumption: a 70% 30-day mortality in the control group and a 20% relative risk reduction for each intervention (early CRRT and beta-blocker). The estimate of the intervention’s effect size was based on clinical expertise and the clinical significance of an intervention, no loss of follow-up or crossover, and 5% type I error and 20% type II error. We assume no interaction between interventions, as the overlap of the time of interventions would be limited and no carry-on effect expected. A total of 496 patients (248 per group) are required for each arm.

To achieve adequate participant enrolment to reach the target sample size, the study will be conducted at 10 high-volume centers in China. A smartphone application has been developed to facilitate randomization at the emergency room.

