## Discussion

Being one of the most seriously ill groups in clinical practice, with high mortality and requiring heavy use of critical care resources, there are considerable challenges to generate reliable evidence to guide the management of ECMO patients. Our ELITE trial attempts to address two important clinical questions with strong pathophysiological mechanisms.

A multicenter retrospective cohort study has shown that FO is common in a pediatric population (peak FO ≥ 10% in 84.8%, ≥ 20% in 67.2%, and ≥ 50% in 29%) [20] where FO has consistently been shown to be associated with adverse outcomes [21–23], while a meta-analysis of observational studies has shown lower mortality in those who receive CRRT [24]. These data suggest that early initiation of CRRT to avoid FO in the context of ECMO may be beneficial. The Kidney Interventions During Membrane Oxygenation (KIDMO) study showed that CRRT use was 43%, 16%, and 35% of patients for FO, for FO prevention, and for AKI, respectively, after ECMO [25]. However, there has not been a randomized trial to support these approaches. So, we designed this ELITE trial. As the closing of arm B, the question of whether beta-blocker is efficient in patients with ECMO remains unaddressed, and more effects should be made.

Other limitations of our trial include the lack of blinding, and for practical reasons, recruitment has been slow due to the small number of patients receiving ECMO despite the expectation of a least 10 cases treated annually across our network of 30 ICUs in China. We did not stratify our randomization by ECMO centers but will perform a subgroup analysis to explore the effect between small and large centers.

In summary, the ELITE trial is the first randomized controlled trial of critically ill patients receiving ECMO support, powered to test the effects of early CRRT versus conventional timing of CRRT on 30-day mortality. The results should inform the management of this important patient group.

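### Randomization is stratified by age and ECPR, but the primary log-rank test is stated without those strata, which costs some power if the factors predict death

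*Protocol article*

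**What the plan says.** - Protocol article, Randomization: "All eligible patients are centrally randomized in a 1:1 ratio", and the schedule is "stratified by age (< 65 vs. ≥ 65 years) and implantation of ECMO for extracorporeal cardiopulmonary resuscitation (yes vs no"). That makes four strata.
- Protocol article, Outcomes: "The proportion of all-cause mortality at 30 days will be compared between the intervention and control groups".
- Protocol article, Statistical analysis: "The primary outcome will be compared between the groups in a log-rank test". No strata or covariates are named. Age and ECPR reappear only in the subgroup paragraph: "The main analysis for each subgroup will be an unadjusted test of interaction in a logistic model".
- Protocol article, Sample size: the assumptions are "a 70% 30-day mortality in the control group and a 20% relative risk reduction for each intervention", with 5% type I error, 80% power, and 496 patients (248 per group) for each comparison.
- Protocol article, Trial status: 89 patients are enrolled in study A, and a feasibility review is due at the end of 2022.

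No section carries the randomization strata into the primary comparison.

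**The concern.** Stratified allocation makes the groups alike on age and ECPR. If those factors predict death, this removes part of the chance variation in the group difference. The ordinary log-rank variance still counts that part, so the test divides by too large a standard error. It then rejects a true null less often than 5% and misses some real effects. A test that sums its numerator and variance within strata does not have this problem.

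What is at stake is a modest amount of power, plus a mismatch between how patients are allocated and how they are compared. Power matters more than usual here because recruitment is slow.

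**Working it through.** **Step 1: the plan's own figure.** Two proportions, 0.70 and 0.70 × 0.80 = 0.56, two-sided 5%. With p̄ = 0.63:

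n per group = [1.960·√(2·0.63·0.37) + z_β·√(0.70·0.30 + 0.56·0.44)]² / 0.14²

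- 80% power (z_β = 0.842): 186 per group, 372 in total.
- 90% power (z_β = 1.282): 248 per group, 496 in total.

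So 496 does not reproduce at the stated 80%; it matches 90%. That is a separate matter, but it means a plain test at 496 starts well above 80%. For the log-rank test, HR = ln(0.44)/ln(0.30) = 0.682 and expected deaths = 248 × (0.70 + 0.56) = 312.5. Schoenfeld power is then Φ(√312.5/2 × |ln 0.682| − 1.960) ≈ 92%.

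**Step 2: assumptions the article does not supply.** 35% aged 65 or over and 25% ECPR, independent of each other; permuted blocks of 4 within strata; exponential death times censored at day 30. Stratum weights w are 0.65·0.75 = 0.4875, 0.35·0.75 = 0.2625, 0.65·0.25 = 0.1625 and 0.35·0.25 = 0.0875. Relative hazards h are 1, HR_age, HR_ECPR and their product. The baseline λ solves Σw(1 − e^(−λh)) = 0.70, and the common treatment hazard ratio c solves Σw(1 − e^(−λhc)) = 0.56. Overall mortality is therefore always the plan's 70% and 56%.

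**Step 3: the two tests.** With U = Σd(g − n₁/n) and V = Σd(n₁/n)(1 − n₁/n), the plain test rejects if U²/V > 3.841. The stratified test computes U and V within each stratum and rejects if (ΣU)²/ΣV > 3.841.

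**Step 4: results at N = 496** (20,000 null and 8,000 alternative replicates).

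| HR age / ECPR | Control mortality by stratum | Null rejection, plain → stratified | Power, plain → stratified |
|---|---|---|---|
| 1.0 / 1.0 | 70% in all | 5.2% → 5.1% | 92.0% → 92.0% |
| 1.3 / 1.3 | 64, 74, 74, 83% | 4.9% → 5.1% | 92.7% → 93.0% |
| 1.5 / 1.5 | 61, 76, 76, 88% | 4.6% → 5.1% | 92.8% → 93.6% |
| 1.5 / 2.0 | 59, 74, 83, 93% | 4.3% → 5.0% | 93.4% → 94.9% |
| 2.0 / 2.0 | 56, 81, 81, 96% | 3.7% → 5.0% | 93.7% → 96.2% |

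Monte Carlo standard errors are √(0.05·0.95/20,000) ≈ 0.15 points for null rejection and √(0.93·0.07/8,000) ≈ 0.3 points for power. Both tests were run on the same simulated trials.

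**Step 5: a smaller trial.** Same assumptions, N = 200, 5,000 replicates. Power, plain → stratified:

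- HR 1.5/1.5: 58.1% → 60.0% (+1.9 points).
- HR 1.5/2.0: 57.7% → 61.7% (+4.0 points).
- HR 2.0/2.0: 58.9% → 64.8% (+5.9 points).

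Over totals of 150 to 250, the gain at HR 1.3/1.3 is 0 to 0.5 points. At HR 1.0/1.0 the two tests differ by at most 0.7 points, which is within simulation error.

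**Step 6: sparse strata.** The smallest assumed stratum (8.75%) holds about 0.0875 × 496 = 43 patients at full size, 0.0875 × 200 = 17.5 at 200, and 0.0875 × 89 ≈ 8 at the reported enrolment.

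**The case against.** The best counter-argument is that the article never says the test is unstratified. Its only use of the word unadjusted concerns the subgroup interaction test. It condenses a fuller protocol, and an unseen analysis plan may already add the strata. This limits confidence about what will be done. It does not remove the point, because the article does more than stay silent: it names the primary test and gives the stratification factors another role.

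The second argument is size. No stratum mortality is given, and nothing is lost if the factors are not prognostic. At 496 patients the plain test already has 92% power or more on the plan's own rates. All of this stands, and it is why the point is modest. If the 30-day proportion were compared instead, the gain would be smaller still. In a simulation of 372 patients with assumed stratum mortality from 60/70/75/85% to 50/70/80/92%, power rose only from 78–79% (chi-square) to 79–80% (Mantel-Haenszel).

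Several stronger readings are tempting but unsupported:

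- A reader might infer that the factors were chosen as strong predictors of death. The Randomization section gives no reason for choosing them.
- A reader might size the gain at 372 patients, where it reaches 3.6 points (86.1% → 89.7% at HR 2.0/2.0). The planned number is 496.
- A reader might call stratification the only power available without more patients. Table 1 shows APACHE II and SOFA collected at randomization, so covariate adjustment is another source.
- A reader might add centre to the criticism. The Discussion says "We did not stratify our randomization by ECMO centers but will perform a subgroup analysis to explore the effect between small and large centers". That is an exploration of effect by centre size, listed among limitations; it is not offered as a cure for imbalance. Under central randomization, chance imbalance between centres does not bias the test.
- A reader might say the confidence intervals will be too wide. The article names no primary effect measure or interval.

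**Conclusion.** The mismatch is in the text, and its direction is clear: if age and ECPR predict death, the plain log-rank test is conservative and less powerful than the stratified one. A reader might infer that the primary result would be invalid. It would not, because the error rate falls below 5%, never above it for this reason.

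The size depends on assumed shares (35% and 25%), blocks of 4, exponential death times and hazard ratios of 1.0 to 2.0 per factor. On those, null rejection by the plain test runs from about 5% to about 3.7%. Stratifying gains about 0 to 2.5 power points at 496 patients and about 0 to 6 near 200. The second range is the more relevant one if enrolment, at 89, stays slow, but even 6 points would not rescue an under-recruited trial. This is a worthwhile, low-cost improvement to a stated test.

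**What to change.** In the Statistical analysis section, name the primary test as a log-rank test stratified by age group (under 65, 65 and over) and ECPR (yes, no), using the strata as recorded at randomization. Report a Cox hazard ratio stratified by the same factors, with its 95% confidence interval. Keep the unstratified log-rank test as a sensitivity analysis. If the analysis plan already does this, align the published text with it. Settle the choice before any comparison by group is seen.

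The cost is a sentence or two of text, with no new data or patients, since both factors are needed to randomize. There are two small downsides. The stratified hazard ratio is a conditional effect (within strata) and should be labelled as such. If enrolment stays low, sparse strata could cost a trivial amount of information.

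### 365-day all-cause mortality is left to a chi-square test on non-missing values, which discards the known survival time of patients not reached at one year

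*Protocol article*

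**What the plan says.** The Outcomes section makes 30-day all-cause mortality the primary outcome and then lists the others: "Secondary outcomes are all-cause mortality at 365 days" comes first, ahead of long-term renal replacement, weaning, quality of life, lengths of stay, readmission and cause-specific death.

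The Statistical analysis section sets the tests in two sentences. For the primary outcome: "The primary outcome will be compared between the groups in a log-rank test". Everything else falls under one general rule: "Other efficacy and safety endpoints will be reported with the *t* test or Wilcoxon test, and the chi-square test for continuous and categorial variables". In full, the rule ends "and the chi-square test for continuous and categorial variables, respectively, as appropriate". On incomplete data it says: "The missing values will not be imputed unless substantial". It gives no threshold for substantial and no imputation method. It then adds: "The number of observations used in the analysis will be reported". A denominator below the number randomized is therefore foreseen.

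Table 1 shows no scheduled visit between day 30 and day 365, and the window at day 365 is ±35 days. The Data management section says that follow-up may be by telephone, face to face or remote consultation.

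**The concern.** Dead or alive at 365 days is a categorical outcome, so the general rule sends it to chi-square. The same event, death from any cause, thus gets a method that can use censored follow-up at 30 days, when little loss is likely. At 365 days, when loss is most likely, it gets one that cannot.

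The two kinds of patient are then treated differently. A death on day 10 is known and is counted. A patient discharged alive, reached on day 200 and not reached at day 365 has no day-365 value, and without imputation leaves the analysis; 200 days of known survival are lost. Only patients last known alive can become missing, so a proportion among those with a known status tends to remove survivors and keep deaths. The one-year mortality reported for each group could be too high and the risk difference somewhat too small. If loss differed between the groups, which is possible in an open-label trial, part of the difference could come from follow-up alone.

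**Working it through.** **Inputs from the article.** 248 patients per group (Sample size); two-sided 5% level (Statistical analysis). The article gives no 365-day mortality and no loss rate at one year. The assumption of no loss in the Sample size section belongs to the 30-day calculation. There is therefore no planned figure for this endpoint to reproduce, and 248 is used only as the group size. (For 70% vs 56%, a two-sided 5% comparison of proportions needs 186 per group at 80% power and 248 at 90%. That is a separate matter on which nothing here depends.)

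**Assumptions.** True 365-day mortality M of 70%, or 75% vs 63% where an effect is assumed; a share l of survivors, 5 to 30%, not reached at day 365.

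**1. Mortality among patients with known status.** All deaths are known and a fraction l of survivors is dropped:

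observed = M / [M + (1 − M)(1 − l)]

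| Survivors lost | M = 70% | Excess (points) |
|---|---|---|
| 5% | 0.70/0.985 = 71.1% | 1.1 |
| 10% | 0.70/0.970 = 72.2% | 2.2 |
| 20% | 0.70/0.940 = 74.5% | 4.5 |
| 30% | 0.70/0.910 = 76.9% | 6.9 |

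**2. Equal loss with a true effect, 75% vs 63% (12.0 points).**

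- 10% lost: 0.75/0.975 = 76.9% vs 0.63/0.963 = 65.4%; difference 11.5 points.
- 20% lost: 0.75/0.950 = 78.9% vs 0.63/0.926 = 68.0%; difference 10.9 points.
- 30% lost: 0.75/0.925 = 81.1% vs 0.63/0.889 = 70.9%; difference 10.2 points.

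The odds ratio does not move. The factor (1 − l) cancels, leaving (0.63/0.37)/(0.75/0.25) = 0.568 throughout.

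**3. Type I error, true mortality 70% in both groups, 248 per group.** With equal loss of 10% or 20%, simulation (200,000 runs) gives 5.0%. For survivor loss of 5% vs 20%:

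- Expected denominators: 248 × 0.985 = 244.3 and 248 × 0.940 = 233.1.
- Spurious difference: 74.5% − 71.1% = 3.4 points.
- Pooled proportion: 347.2/477.4 = 0.727; standard error √[0.727 × 0.273 × (1/244.3 + 1/233.1)] = 0.0408.
- Shift: 0.0340/0.0408 = 0.834. Rejection probability: P(Z > 1.126) + P(Z < −2.794) = 13.3%; simulation gives 13.2%.

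The same calculation gives 5.8% at 5% vs 10% (5.9% by simulation). By simulation the error is 8.4% at 5% vs 15%, 20.4% at 5% vs 25% and 21.7% at 10% vs 30%. At 5% vs 25%, the missing share of randomized patients is 0.30 × 5% = 1.5% and 0.30 × 25% = 7.5%, or 4.5% overall.

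**4. When the direction holds.** Let L be the share of randomized patients with unknown status and q the share of them who in fact died by day 365. The observed proportion is (M − Lq)/(1 − L), which exceeds M exactly when q < M. At M = 70% it is enough that those not reached are mostly alive; if more than 70% of them died, the direction reverses.

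**5. The alternative under non-informative loss.** One million simulated patients, 63% dead by day 30 and 70% by day 365, with loss after day 30 at probability 10, 20 and 30%: the complete-case proportion is 72.1, 74.2 and 76.6%. Kaplan-Meier with censoring at last contact gives 70.0% each time.

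**The case against.** **The rule is general and qualified.** No sentence names chi-square for 365-day mortality or says that patients of unknown status are dropped, and the text leaves room for imputation and for choosing the test as appropriate. This softens the point without removing it. The second qualifier chooses among t, Wilcoxon and chi-square, none of which uses censored follow-up. The first has no threshold, and the 5% vs 25% case shows marked error with only 4.5% missing overall.

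**Censoring rules belong in the analysis plan.** Their absence from a condensed article is no fault. The point here is narrower: the article states a method for this class of endpoint, and the method suits this one poorly.

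**Follow-up may be good.** Several contact routes, a wide window at day 365 and encouragement to attend should reduce loss. At 5% of survivors lost the overstatement is about 1 point.

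**The false-difference figures need clear imbalance and full enrolment.** This stands. No passage suggests that loss will differ between the groups. The Trial status section reports 89 patients enrolled in study A; at about 44 per group, the 5% vs 20% and 10% vs 30% cases give type I errors of only about 6.4% and 7.9%.

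**The direction is not certain.** This also stands. Some discharged patients may die unreached, and if many do, censoring at last contact is informative and the Kaplan-Meier estimate is biased too.

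**Intention to treat.** A reader might infer that dropping patients contradicts the plan's own principle. The sentence reads: "All patients will be analyzed in accordance with the results of randomization, regardless of whether they received the prescribed therapy". It settles which group a patient is counted in when treatment was not followed; it does not speak to missing outcomes. There is no contradiction.

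**Conclusion.** The point holds in a limited form. As written, one-year all-cause mortality goes to a test on non-missing values, which keeps every known death and loses the known survival of patients not reached. Three results follow, all resting on assumed rates:

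- If those not reached are mostly alive, 365-day mortality is overstated by about 1 to 7 points (true 70%, 5 to 30% of survivors lost).
- Equal loss does not inflate the type I error. A true risk difference shrinks slightly, from 12.0 to 10.9 points at 20% loss with 75% vs 63%, and the odds ratio is unchanged.
- Unequal loss can create a false difference: about 6% type I error at 5% vs 10% of survivors lost and about 13% at 5% vs 20%, with 248 per group.

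Two stronger readings are tempting: that the plan is bound to overstate mortality, and that it will produce false positives. The documents support neither, because they give no loss rate, no sign of imbalance and nothing on the fate of patients not reached. The endpoint is secondary and the primary analysis is not affected. The change is still worth making, since a better method is already planned for the same event at 30 days.

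**What to change.** State that all-cause mortality at 365 days is analysed as time from randomization to death in all randomized patients, censored at the date last known alive or at day 365, whichever comes first. Report Kaplan-Meier mortality at day 365 by group, the difference with a 95% confidence interval, and a log-rank or Cox comparison. Add a sensitivity analysis for unknown vital status that varies the assumed mortality of patients not reached in each group, because censoring is itself biased if lost patients die more often. Keep chi-square for categorical endpoints without censoring.

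The cost is a sentence or two in the analysis section and one added sensitivity analysis. The planned log-rank test already needs dates of death and of last contact; their collection has only to run to day 365. No extra patients or procedures are required, and with enrolment in study A reported as ongoing, the wording can be settled before any analysis.
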